# THE NEED FOR A TRIAL

## What is the problem to be addressed?

We propose a cluster randomized trial to determine which surface (engineered wood fibre or sand) better protects children from upper extremity fractures from school playground falls.

Fully 60 percent of Canadian children’s Emergency Department (ED) injury visits result from sports and leisure activities(1). Playground equipment injuries alone comprise ten percent of ED injury visits among 5 to 9 year old Canadian children (2). At Toronto’s Hospital for Sick Children from 1997 to 2002, 739 upper extremity fractures were seen from playground equipment falls, of which 331 (45%) required operative reduction. By comparison, 353 upper extremity fractures were seen from standing height playground falls, of which 49 (14%) required operative reduction (data source: Canadian Hospitals Injury Reporting and Prevention Program, CHIRPP, unpublished). In the US (3), a prospective cohort study found that playground injuries had a higher severity than any other child injury mechanism except transportation. This study also found that the admission rate (8%) for playground injuries was higher than that for any other child injury mechanism except transportation. Phelan (4) reported 920,000 emergency department visits in the US from 1992 to 1997 resulting from playground equipment falls, and concluded that “interventions targeting schools and 5 to 9 year old children may have the greatest impact on reducing emergency visits for playground injuries.” Chalmers (5), in a study in New Zealand, demonstrated that optimizing falling height and surface conditions would decrease playground injury ED visits by 45%.

The major determinants of playground injury reported consistently in case control studies are fall heights greater than 1.5 metres and poor surfacing. Falls of 1.5 metres and up had 2.0 to 4.1 times higher odds of significant injury than lower falls (5,6). Lack of impact absorbing surfaces increased injury odds 2.3 times in a New Zealand study (5). In Kingston Ontario, injury odds were 18 times higher for a fall onto a surface which did not meet CSA impact absorption standards (7).

Current CSA standards for playground surfaces can be met using permanently installed ground rubber, wood chips/wood fibers, or sand. Permanently installed rubber is too expensive for routine use in Toronto schools, but wood fiber and sand are both used routinely. Mechanical testing with dropped headforms favours wood fibre, but epidemiological evidence favours sand. The surfaces have never been compared in a study using injury as an outcome. To date, there have been no systematic reviews nor randomized trials addressing playground surfacing.

Surfacing type and depth standards are based on laboratory assessment of the maximum fall height before a fatal (200G) acceleration of a dropped headform occurs. This height is 11 feet for wood chips and 8 feet for fine sand (8). Wood fibre also has better impact attenuation performance than sand when wet or frozen (9). Surfacing standards, however, are not based on any epidemiological evidence or actual injury experience (5,10,11).

Real world playground injuries rarely conform to the test scenario of a direct fall producing a fatal head injury. The most common severe playground injuries are upper extremity fractures, which occur when a child falls onto an outstretched arm. Lower friction surfaces which permit the arm to slide decrease the fracture risk (12). Sand is both significantly softer and lower friction than engineered wood fiber playground surfaces (13). Falls onto sand playgrounds had the lowest injury rates (7 per 10,000 student years), compared with higher friction surfaces such as gravel (15/10000), grass (12/10000), mats (16/10000), or asphalt (44/10000) (14). Sand surfaces were associated with lower severity playground injuries than other surfaces in a Montreal study (15) and in this study neither fall height nor impact attenuation alone influenced injury severity. Decreased injury risk on low friction surfaces is also well documented for football (16,17), indoor handball (18), and army obstacle course training (19). By contrast, wood (bark) surfaces under playground equipment (10,11) had as high, or higher a fracture rate than concrete. In this study of 30,000 children, fracture rates were adjusted for exposure to play on each surface type. The vast majority of the fractures were upper extremity fractures.

**Rationale:** Loose fill playground surfaces are popular because they are an inexpensive way of meeting impact attenuation standards. Physical and epidemiological studies suggests that fractures may occur more often on higher friction fills (wood fibre) and less often on lower friction fills (sand), but the surfaces have never been compared using injury rates as an outcome. Real world performance of the surface will also depend on its behaviour in wet, frozen, or snowy conditions and on how children play in that particular surface. The most meaningful test of effectiveness of a surface is injury rates during real world use. A unique opportunity exists to perform a randomized trial which will guide standards development and allow evidence based injury prevention. This is the first randomized trial of a playground injury prevention intervention, is methodologically unique, and will lead directly to improved standards and improved health.

## What are the principal research questions to be addressed?

### Primary research question:

Is there a difference in playground upper extremity fracture rates in schools with Fibar® (wood fibre) surfacing compared to schools with granite sand surfacing?

### 1.2.2. Secondary research questions:

Are there differences in overall playground injury rates and in head injury rates in school playgrounds with Fibar® (wood fibre) surfacing compared to school playgrounds with granite sand surfacing?

## Why is a trial needed now?

Despite the importance of playground injuries, to date, there are no randomized trials of injury countermeasures. Published intervention studies are pre post studies without injury outcomes. Therefore, they cannot be used to guide decision making. By examining injury rates by type of surface, it may be possible to dramatically reduce the numbers and severity of children’s playground injuries. Last, there is a unique opportunity to perform this study within an existing program of playground replacement carried out by the Toronto District School Board. This means that a high quality randomized trial can be conducted with high leverage and modest cost. In the summer of 2000, the Toronto District School Board (TDSB) removed playground equipment that did not comply with newly revised Canadian Standards Association (CSA) standards (20). Subsequently, there has been a phased replacement of equipment. In the spring of 2003, retrofitting and replacement of equipment began in 37 school playgrounds that had partial equipment removal. Both wood (Fibar®) and granite sand surfaces are routinely used in TDSB schools. The Toronto District School Board agreed to randomize surfacing for these 37 schools, allowing an ideal opportunity to determine the relationship between surface type and playground injury rates. The $1.7M cost of replacing the playgrounds according to the randomization schedule was covered by the TDSB. Playground injuries can be identified from a prospectively recorded population based database (Ontario School Board Insurance Exchange - OSBIE). The playgrounds have a service life of 10 to 20 years, so outcomes from this randomized cohort can be assessed once funding is secured.

## Relevant Systematic Reviews

None (Medline, Cochrane, bibliographies of retrieved studies)

## How will the results of this trial be used?

Evidence from the trial will be incorporated into the next revision (2008) of the Canadian Standards Association standard for playgrounds, ensuring translation into action across Canada. [name] has presented to the CSA subcommittee on sports and leisure injuries in the past. There are thousands of school and municipal playgrounds across Canada which have loose surfaces that require regular maintenance and replacement. Evidence regarding the effectiveness of different surfacing materials will allow determination of the safest physical environment for Canadian children

Results of the trial will be shared with the Toronto District School Board as pre-arranged, and offered to the City of Toronto Department of Parks and Recreation and the Ontario Ministry of Education. The Ontario School Board Insurance Exchange will forward results to all school boards in Ontario and to their counterparts in other provinces. We also anticipate that there will be media interest in the results of this study. The Hospital for Sick Children’s Public Affairs Department will assist the investigators in developing a press release and media strategy. Safe Kids Canada, the leading knowledge translation organization for children’s injury prevention, will convey the results to its over 1500 partner organizations in communities across Canada. In addition, results of the trial will be published in a leading international journal and presented at the World Conference on Injury Prevention and Control.

# THE PROPOSED TRIAL

## What is the proposed trial design?

A two arm, cluster randomized trial of the effect of playground surface on playground injury rates will be performed. 37 Schools have been randomized, 19 to receive a wood fibre (Fibar®) playground surface and 18 to receive a granite sand playground surface. Playground injuries will be recorded prospectively for two school years following the intervention.

## What are the planned trial interventions?

### Fibar®

Manufacturer’s guidelines report that Fibar® is a shredded, Engineered Wood Fibre® that is guaranteed to perform for 20 years. It does not decompose and is not chemically treated. Fibar® is certified by the International Play Equipment Manufacturers Association (IPEMA) in accordance with ASTM F1292-99 and CAN/CSA Z614-98 impact tests. Fibar® is a component of the Fibar System 300®. This consists of wood fibers compacted to a specified depth (usually 12”) over FibarFelt® (100% polyester, non-woven geotextile fabric) and FibarDrain® drainage system. FibarMats® (rubber mats) are placed under each swing, slide exit and sliding pole.

Specific installation and maintenance instructions ensure that the material is properly distributed, properly drained, and topped up to maintain correct impact attenuation. Fibar is currently the most popular surfacing for newly replaced Toronto school playgrounds. However, the concerns raised by Mott (10,11) about the fracture rates on bark chips (equal to that on concrete) may possibly apply to Fibar because the materials are physically similar.

### Granite Sand

Granite sand consists of sub-angular or sub-rounded grains made from naturally weathered granite rock. It is washed to be free of all organics and silt and clay contaminants. It has a percolation rate greater than 30 inches per hour, allowing for excellent drainage. Granite sand is compliant in accordance with ASTM F1292-99 and CAN/CSA Z614-98. Manufacturer’s guidelines report that granite sand does not compact, does not react with water to form a hard surface and does not require rototilling. When children run in the sand, they push it back into the high traffic hollows that tend to form under swings and the bottom of slides, reducing the required maintenance in these areas.

Installation requires attention to drainage and depth. Maintenance involves daily inspection and occasional cleaning.

## What is the allocation method?

A computer generated random number list was used to assign the 37 participating schools to Fibar® or granite sand groups. School level covariates including student population, socioeconomic status, and playground size are balanced between the groups as shown in table 1 below:

Table 1: Results of Randomization:

|  | **Fibar Schools**  **N = 19**  **Mean (S.D.)** | **Granitic Sand Schools**  **N = 18**  **Mean (S.D.)** | **P-Value** |
| --- | --- | --- | --- |
| Number of Students | 409.2 (312.1) | 416.3 (195.4) | 0.934 |
| Learning Opportunities Index (LOI) | 0.55 (0.27) | 0.49 (0.29) | 0.533 |
| Size of Playground (m2) | 18826.6 (22657.1) | 17142.8(22589.3) | 0.835 |
| TDSB Budget ($) | 42914.6 (31086.8) | 48658.70 (27426.2) | 0.555 |
| Cost of re-surfacing ($) | 7073.68 (1442.55) | 5688.9 (1179.9) | 0.003 |

Note: The TDSB Learning Opportunities Index 2002-03 combines information from the following variables: average and median income of families with school-aged children; parental education; proportion of lone-parent families; recent immigration; housing type (apartment, single detached housing); student mobility. It is the standard socioeconomic status measure for TDSB schools.

## What are the proposed methods for protecting against other sources of bias?

### Observer Bias

Identification of injuries is via Ontario School Board Insurance Exchange (OSBIE) incident report forms which are filled out by teachers. All schools use the same forms and have the same written policy for when a report is required (‘when someone needs medical or dental attention’). Inservices will take place at each school to remind teachers and staff of the threshold and process of completing the reports. Follow up of incident reports by a research assistant will rely on parent report of the injury type and severity. We do not anticipate that the accuracy of parent report will differ by surface type. The parent interview will be based on the Canadian Hospital Injury Research and Prevention Program (CHIRPP) questionnaire. CHIRPP is a national ED based injury surveillance system. With participation by all 10 Canadian children’s hospitals, CHIRPP injury data (provided by parents and physicians) have been shown to be reliable and valid (21-23). Finally, the primary outcome is upper extremity fractures, which we believe will be consistently reported across schools due to their severity.

### Co-interventions

The playground resurfacing program is part of a larger program that will also bring playground equipment up to CSA standards. Therefore, there may be modification of play structures within playgrounds. Such modifications, however, will be similar and randomizing the intervention will balance such cointerventions. We know that the total cost of replaced equipment is balanced between groups (table 1 in sec. 2.3). Actual equipment present at each playground will be surveyed, photographed, and measured (see appendix). Installation and maintenance of both surfaces will be done by the same TDSB employees working to CSA standards. Maintenance may differ systematically between groups if one surface is more costly or difficult to maintain, so actual surfacing depths will be measured during the followup period and treated as covariates.

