### Covariates

School population, playground size, socioeconomic status, and number of hours of play may influence injury rates although such effects would be independent of surfacing so it is simply necessary to balance the groups. The randomization has already been performed and school population, playground size, and socioeconomic status are balanced as would be expected with 37 clusters (see table 1 in sec 2.3). At each school, supervised outdoor play occurs for equal mandated time periods (totaling 2 hours) each day, weather permitting. Intensity of supervision will be addressed by calculating the student to teacher ratio at each school according to the playground supervision roster.

Weather will be the same for all schools, but it is possible that effect modification (different injury risks by surface in wet vs dry weather, or when frozen) could occur. Accordingly, rainfall and snowfall amounts will be recorded from Environment Canada web records and will be used in a secondary analysis as described below.

Depth of undersurface measurements will be done three times per year (September, January and June) of surfaces at all schools at falling points and slide exits. Falling heights will be recorded by surveying the equipment using diagrams and digital photos, and asking parents for the location of any injury fall. Depth measurements and falling heights will be used as covariates in the analyses (see appendix).

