## Give details of the planned analyses

### Primary outcome:

The primary analysis will include all randomized schools and upper extremity fractures as defined in Section 2.8.1. This effectiveness analysis will compare the rates of injuries in the two groups. A poisson model will be used since the outcomes are counts. For each school we will observe X, the number of injuries reported over the two-year period, and Y, the student-years accumulated over the two-year period. The estimated injury rate for each school is X/Y, with estimated variance X/Y2. Using methods proposed by Thompson et al. (27), an overall injury rate for each type of school (Fibar® or granite sand), along with the corresponding variances will be estimated. This method accounts for the extra variation due to the clustering. The injury rates can then be compared by a Z-statistic which is the difference in the two rates divided by the square root of the sum of the corresponding variances. Covariate adjustment for school level variables such as average age, proportion of males, school size, socioeconomic status, and surface depth will be facilitated using methods given by Raudenbush (28).

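### Surfacing depth measured after allocation is in the primary-outcome adjustment set, and the protocol does not say whether the adjusted or the unadjusted result is primary

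*Protocol*

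**What the plan says.** Depth enters the plan as a covariate in three places in the Protocol.

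- **Co-interventions.** The reason given is that "Maintenance may differ systematically between groups if one surface is more costly or difficult to maintain". The remedy chosen is adjustment for measured depth, in these words: "so actual surfacing depths will be measured during the followup period and treated as covariates".
- **Covariates.** Depth is measured at every school in September, January and June, at falling points and slide exits. Falling heights come from a survey of the equipment and from "asking parents for the location of any injury fall". The section concludes: "Depth measurements and falling heights will be used as covariates in the analyses (see appendix". Weather, by contrast, is expressly assigned to a secondary analysis.
- **Planned analyses, Primary outcome.** Arm-level injury rates are first compared by a Z-statistic with no covariates, in what the section calls an effectiveness analysis. It then provides for adjustment for "school level variables such as average age, proportion of males, school size, socioeconomic status, and surface depth". It does not say which of the two results is the primary one.

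The target is stated elsewhere. The Contamination section commits to intention to treat among the randomised schools, and the Rationale says: "The most meaningful test of effectiveness of a surface is injury rates during real world use".

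**The concern.** Depth during follow-up is not a baseline characteristic. The protocol adjusts for it precisely because it may come to differ between arms through the cost or difficulty of maintaining the assigned material. A variable with that history may lie on the path from surface to injury. Conditioning on it answers a different question, namely how the surfaces would compare had they kept the same depth. It also gives up the protection of randomisation for the adjusted estimate, because anything that affects both depth and injuries (intensity of play, for example) can then bias the comparison.

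How well a surface holds its depth in use is part of the real-world performance that the trial sets out to measure. If the adjusted result were reported as the main one, the answer passed to the standards body would not be the randomised one. With two candidate results and no stated order, the choice could also be made after the data are seen.

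**Working it through.** **1. The plan's own sample size.** Inputs from the sample-size section for the primary outcome: rates of 0.004 and 0.002 per student-year, y = 820 student-years per school, k = 0.2, alpha 0.05 (two-sided assumed; one-sided gives 13.5 and does not match), power 80%. The formula itself does not appear in the text as read. The usual unmatched form for rates is

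c = 1 + (z_α/2 + z_β)² × [(λ0 + λ1)/y + k²(λ0² + λ1²)] / (λ0 − λ1)²

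= 1 + 7.849 × [0.000007317 + 0.0000008] / 0.000004 = 1 + 7.849 × 2.029 = 16.93.

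This rounds up to the stated 17 per arm. No covariate enters, so the trial is sized on the total, unadjusted effect. With 37 schools (18.5 per arm on average) the non-centrality is √(17.5/2.029) = 2.937 and power is Φ(2.937 − 1.96) = 84%.

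**2. What depth adjustment does to the estimand.** The documents give no share of the effect acting through depth, so the share m is assumed. The depth-adjusted ratio is exp[(1 − m) ln 0.5]:

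- m = 10%: 0.54; formula power 77%
- m = 25%: 0.59; formula power 64%
- m = 50%: 0.71; formula power 36%
- m = −25% (depth works against the surface effect): 0.42; formula power 94%

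The last line matters: adjustment can exaggerate the effect as well as shrink it. These powers are before any loss from correlation of depth with arm.

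**3. Cost of correlation alone.** Suppose the arms differ in depth by 1 within-arm SD (assumed). With near-equal arms, R² = 0.25/(0.25 + 1) = 0.20. Power is Φ(2.937 × √0.80 − 1.96) = Φ(0.667), about 75%, even with no mediation.

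**4. Simulation.** 19 and 18 schools, 820 student-years each, k = 0.2, total ratio 0.5, a 1-SD depth difference, overdispersed Poisson model, 2,000 runs per row:

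| Assumed share via depth | Unadjusted ratio (power) | Depth-adjusted ratio (power) |
|---|---|---|
| 0% | 0.496 (86%) | 0.493 (77%) |
| 25% | 0.496 (84%) | 0.588 (53%) |
| 50% | 0.495 (78%) | 0.699 (28%) |

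The unadjusted analysis recovers the total effect throughout. The adjusted one drops whatever acts through depth, and it loses power even when nothing does.

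**5. Which school variables are safe to adjust for.** Table 1 includes a TDSB budget line. Its total is 19 × 42,914.6 + 18 × 48,658.7 = about $1,691,234, essentially the $1,691,210 replacement cost in the section on trial cost and duration. The section on why a trial is needed now describes that replacement as following the randomisation schedule. The budget is therefore not shown to be independent of allocation. Resurfacing cost differs by arm in Table 1 ($7,073.68 against $5,688.9, p = 0.003), as it would if it depends on the material.

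**The case against.** The strongest reply is that the total effect is not lost. The analysis section specifies the unadjusted Z-comparison first, over all randomised schools, and calls it the effectiveness analysis. The Contamination section states intention to treat, and the sample size rests on the unadjusted effect. This stands. A reader might infer that the trial's only answer would be a depth-adjusted one; the document does not say so. What remains is that depth sits among the primary-outcome adjustments without any order of precedence.

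Three further inferences are tempting and unsupported.

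- **That fall height of injured children is entered in the rate model.** The Covariates section also takes heights from an equipment survey, so a school-level height can exist for every school, with or without injuries. The analysis section does not name fall height. Only the height of the injury fall is unusable as a rate covariate, since uninjured student-time has no value for it.
- **That depth will be strongly tied to arm.** The protocol says only that maintenance may differ, and that the same board employees install and maintain both surfaces to one standard. Power would fall to 55% or 26% if arm explained 50% or 80% of depth variance, but with near-equal arms that needs differences of about 2 or 4 within-arm SDs. Nothing in the document suggests either.
- **That adjustment must pull a real difference towards the null.** The direction is unknown.

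It is also fair that an equal-depth comparison has explanatory value, since surfacing standards concern type and depth. That argues for labelling such an analysis, not for forbidding it.

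**Conclusion.** The point holds in limited form. The protocol places a post-allocation variable, which it expects may depend on the assigned surface, in the adjustment set for the primary outcome, and it leaves open whether the adjusted or unadjusted result is primary. The adjusted estimate is a depth-held-constant effect, at odds with the stated real-world, intention-to-treat aim. This is a rule that the protocol itself sets, not a detail left for a later analysis plan.

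The size cannot be established from the document. The shifts from 0.50 to about 0.59 or 0.71 rest on assumed mediated shares of 25% and 50%. The fall in power from the mid-80s to about 75-77% rests on an assumed 1-SD depth difference and no mediation. Because an unadjusted comparison is already specified, this should be fixed, but it does not invalidate the design.

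**What to change.** - In the primary-outcome analysis, name one primary result: the unadjusted intention-to-treat comparison of rates, or one adjusted only for variables fixed before allocation or unaffected by it. Suitable candidates are school size, the Learning Opportunities Index, playground size, and the age and sex mix of the school. TDSB budget and resurfacing cost should not be used.
- Remove surface depth from that adjustment set in the Co-interventions, Covariates and Primary outcome sections. Report depth by arm as a process measure, and label any depth-adjusted model as explanatory.
- In the Covariates section, separate the two kinds of height. School-level equipment height from the survey may stay as a covariate if the assigned surface does not affect it. The height of the injury fall should be described among injuries only and kept out of the rate model.

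The cost is wording only. All planned measurements are still collected, and the sample size does not change.
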